#### Secondary outcomes

Incidence of endoscopic recurrence with a Modified Rutgeerts score ≥i2b at 3 years follow‐up.Incidence of severe endoscopic recurrence (Modified Rutgeerts score ≥i3) at 3 years follow‐up.Clinician and patient‐reported symptomatic recurrence up to 3 years [31].Quality of life (EQ‐5D‐5L) [32] assessed at baseline, 6 weeks and 12 months post‐surgery.Surgical recurrence up to 3 years (clinician and patient reported).Radiological and surgical anastomotic leak as defined by the latest consensus [33]; other complications for each intervention assessed at the time of surgery, 6 weeks and 12 months post‐intervention.

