### Allocation

Once consent has been obtained (Appendix 1), baseline data recorded and eligibility confirmed, participants will be centrally randomised using the CTRU online randomisation system (SCRAM). Randomisation will occur intraoperatively when all eligibility criteria are met. The doctor or research nurse will access the web‐based randomisation system, enter patient demographic details (ID, date of birth) and the treatment allocation will be returned.

Participants will be allocated using a computer‐generated pseudo‐random list, stratified by centre, with random permuted blocks of varying sizes. The sequence will be restricted by authorisation until analyses are complete.

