### Statistical methods

The primary outcome is the time to endoscopic recurrence (ER), over a follow‐up of up to 3 years, defined as a Modified Rutgeerts score [≥i2]. Patients without a reported ER will be censored at their last known date of not having had ER. The primary effectiveness analysis, on the intention‐to‐treat (ITT) sample, will compare the time to ER, between the two factors (Kono‐S vs. standard anastomosis surgery; extended mesenteric resection vs. close mesenteric resection) using a mixed‐effects parametric survival model with random effects for centre and surgeon and fixed effects for the two factors. The model will be implemented using a Weibull survival distribution.

It is anticipated that there will be no interaction between the two factors. To test this assumption, the initial statistical model will include an interaction (Kono‐S (yes or no) vs. extended mesenteric resection (yes or no)) term between the two factors. We will report the estimate of the interaction term and its associated 95% confidence interval (CI).

If the CI for the hazard ratios (HR) for the interaction term shows no evidence of an interaction, then we will analyse the data, without the interaction term, using the simpler factorial design with the two main factors. The CIs for the HRs for the Kono‐S versus standard anastomosis contrast and extended mesenteric resection versus close resection contrasts will be reported from this simpler model. If the CI for the HR for the interaction term demonstrates evidence of an interaction, then we will analyse the data using the four randomised groups separately, with standard anastomosis and close mesenteric resection as the reference treatment. The treatment effects and corresponding 95% CIs will be presented for all relevant comparisons.

We will complement the ITT analysis of the primary outcome with several sensitivity analyses. A per protocol analysis will estimate the efficacy of the Kono‐S versus standard anastomosis and extended versus close mesenteric resection in participants who adhere to the main aspects of the protocol. For participants who do not have a colonoscopy during the trial, or whose Modified Rutgeerts score was not completed, missing data will be imputed through best‐ and worst‐case scenarios to investigate the impact of assuming informative missingness (missing not at random assumptions).

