Secondary endpoints will be analysed as follows: Time‐to‐event outcomes will be analysed as per the primary outcome. Binary outcomes will be compared between the two factors ((1) Kono‐S vs. standard anastomosis and (2) extended vs. close mesenteric resection) using a multi‐level mixed effects logistic regression model with adjustment for baseline covariates, with associated ORs and 95% CIs. Absolute risk differences with 95% CIs will also be presented for binary outcomes. Continuous outcomes will be analysed using a multi‐level mixed effects regression model with adjustment for baseline covariates. All multi‐level models will use the same covariates as the primary analysis model. The serious adverse event (SAE) rates in the post‐randomisation period will be compared between the four randomised groups using a chi‐squared test and 95% CIs for each of the four randomised groups. We will also count the total number of SAEs experienced by each patient and compare counts using a Poisson generalised linear model (GLM) and reporting the risk ratio and associated 95% CIs.

Regardless of the statistical significance of the overall effect, exploratory subgroup analyses will be carried out for the primary outcome (ER). We will carry out subgroup analyses to examine if treatment effects differ based on patient demographics, disease phenotype and medical treatment history. As this trial is not formally powered for subgroup analyses, all subgroup effects will be considered exploratory, and *p*‐values will not be presented.

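### The secondary models borrow their baseline covariates from a primary model that lists none, so EQ-5D-5L might not be adjusted for its own collected baseline

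*Protocol article*

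**What the plan says.** Under Statistical methods, the primary outcome is analysed with a mixed-effects Weibull model that has "random effects for centre and surgeon and fixed effects for the two factors". An interaction between the factors is added in the initial model. No patient-level baseline covariate is named.

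The same section turns to the secondary outcomes. Binary outcomes get a "mixed effects logistic regression model with adjustment for baseline covariates", and continuous outcomes get a "mixed effects regression model with adjustment for baseline covariates". Neither sentence names the covariates. The next statement on the matter is that all multi-level "models will use the same covariates as the primary analysis model".

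Secondary outcomes lists EQ-5D-5L as "assessed at baseline, 6 weeks and 12 months", and Table 1 confirms a baseline measurement. Table 1 also schedules IBD-Control and CDAI at baseline, 6 weeks and 12 months. Allocation states that randomisation is "stratified by centre, with random permuted blocks of varying sizes".

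**The concern.** The secondary analyses are promised baseline adjustment, and the covariates are then fixed by pointing at the primary model. As described, that model has no baseline covariates to point at. Centre and surgeon do not fill the gap: they are random effects for clustering, not patient characteristics measured before treatment. An analyst who follows the primary model as written cannot deliver the promised adjustment. One who adds covariates to make the promise good departs from the primary model as published.

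The practical stake is quality of life. The baseline value is usually the most useful covariate for a continuous outcome measured repeatedly, and here it is already collected. Completing the primary model with prognostic factors for recurrence would not settle this either, because baseline EQ-5D-5L has no natural place in a model for time to endoscopic recurrence. The literal rule would still leave it out. The loss would be precision, and any chance imbalance in baseline EQ-5D-5L would stay in the estimate.

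**Working it through.** **1. The statements side by side** (all in Statistical methods)

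| Model | Terms stated | Patient-level baseline covariates named |
|---|---|---|
| Primary (Weibull) | Two factors, random centre, random surgeon, initial interaction | None |
| Binary secondary | Adjusted for baseline covariates | Not named |
| Continuous secondary | Adjusted for baseline covariates | Not named |
| All multi-level models | Same covariates as the primary model | None, by reference |

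Rows 2 and 3 promise something that row 4, read with row 1, cannot supply.

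**2. The plan's own figures.** The sample size does not depend on covariates, but it can be checked. The stated 1-year risks of 52.5% and 32.5% give HR = ln(0.675)/ln(0.475) = 0.528. Freedman's formula at 90% power and 5% two-sided gives 110.1, rounded up to 111 events, against 112 stated. From 111 events: 2 × 111/(0.525 + 0.325) = 261.2. Multiplying by the design effect 1 + 14 × 0.01 = 1.14 gives 297.7, and dividing by 0.97 gives 306.9, or 153.5 per group. Rounded up, this is the stated 154. From 112 events the same steps give 154.9. The plan's figures hold, and none of them bears on the present point.

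**3. What own-baseline adjustment is worth for EQ-5D-5L.** The correlation ρ between baseline and follow-up is not in the documents and is assumed. Adjustment multiplies the variance of the treatment contrast by 1 − ρ² and the standard error by √(1 − ρ²). The difference detectable with 90% power, in SD units, at one time point with 154 v 154 and ignoring clustering and attrition, is (1.960 + 1.282) × √(2/154) × √(1 − ρ²).

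| Assumed ρ | Variance factor | Variance saved | SE reduction | Detectable difference |
|---|---|---|---|---|
| No adjustment | 1.00 | – | – | 0.37 SD |
| 0.3 | 0.91 | 9% | 5% | 0.35 SD |
| 0.5 | 0.75 | 25% | 13% | 0.32 SD |
| 0.6 | 0.64 | 36% | 20% | 0.30 SD |

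**4. Does a primary model without covariates fall short of the planned power?** Suppose one binary prognostic factor with 40% prevalence and HR 2 or 3 (both assumed), and a control risk of 52.5% at 12 months.

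- If the hazard ratio conditional on that factor is set to 0.528, the treated risk is 33.1% (factor HR 2) or 34.0% (factor HR 3). The marginal HR is then 0.54 or 0.56. Unadjusted power below 90% in that setting belongs to a smaller effect than the protocol assumes.
- To keep the protocol's 32.5%, the conditional HR must be 0.516 or 0.498. The marginal HR is then 0.528, as planned.
- A simulation of 2,000 trials per setting, with 149 per group (154 × 0.97 = 149.4) and the marginal risks held at 52.5% and 32.5%, gave power of 92% unadjusted and 94% adjusted (factor HR 2), and 93% and 96% (factor HR 3). It did not model clustering by surgeon, so the levels are optimistic and only the differences of 2 to 3 points are informative.

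Adjustment could add a little power. The calculation does not show that the plan lacks any.

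**The case against.** The strongest reply is that this is condensation. The article does not say that its list of primary-model terms is exhaustive, and the sentence on shared covariates takes for granted that some exist. The list may sit in the full protocol or the SAP, where such lists commonly belong. That stands as far as a missing list is concerned. It does not remove the mismatch, because the article states the primary terms and then defines the secondary covariates by reference to them.

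Three stronger readings are tempting, and the documents do not support them.

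- A reader might infer that EQ-5D-5L will not be adjusted for its baseline. The sentence on continuous outcomes promises baseline adjustment, and a reading of common terms plus the baseline value is open. Own-baseline adjustment is neither named nor excluded.
- A reader might infer that the primary model is wrong because it omits factors such as primary versus recurrent disease. Randomisation makes the unadjusted comparison valid, and centre, the only stratifier, is in the model. Nor are baseline data ignored: the plan will explore whether "treatment effects differ based on patient demographics, disease phenotype and medical treatment history".
- A reader might infer that the primary comparison is underpowered or its hazard ratio biased towards 1. The difference between adjusted and unadjusted hazard ratios reflects non-collapsibility, that is, two different estimands. The size of any power gain rests on a prevalence and covariate effects that the documents do not give.

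**Conclusion.** The inconsistency is real and can be seen within one section: baseline adjustment is promised and then tied to a model that lists no baseline covariates. The consequence that the text supports is that EQ-5D-5L at 6 weeks and 12 months might go unadjusted for its collected baseline. Under an assumed correlation of 0.3 to 0.6, that would forgo a 9% to 36% reduction in variance. It would not invalidate the comparison.

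This is a free improvement to the secondary analyses. Prognostic covariates in the primary model are an optional gain in precision, not the correction of an error, and the stated 90% power is not called into question.

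**What to change.** Replace the sentence on shared covariates with an explicit rule. Secondary models use the primary model's terms (the two factors, random centre and random surgeon) plus the baseline value of the outcome wherever it is collected. That means EQ-5D-5L, and IBD-Control and CDAI if they are analysed.

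Make the description of the primary model agree, either by naming a short pre-specified list of collected prognostic covariates or by stating that there are none. The wording for binary outcomes should follow the same decision.

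The EQ-5D-5L rule costs only wording, since Table 1 already schedules the data. Adding covariates to the primary model would cost more. It changes the primary analysis and makes the reported HR conditional on those covariates. It also needs a rule for missing baseline values: CDAI, for instance, depends on a 7-day pre-operative diary. Primary versus recurrent disease is not a separate item in Table 1 and would have to come from the medical history. Whichever option is taken, settle it before any unblinded outcome data are seen.

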### Sample size

The primary outcome will be the time to endoscopic recurrence (ER) post‐randomisation (Modified Rutgeerts score ≥ i2). All participants will be followed up for a minimum of 6 months post‐randomisation and up to a maximum of 3 years. The best existing data indicates ER rates of approximately 65% on conventional surgery and 24% on Kono‐S surgery at 12 months [34]. Other published data on the rate of endoscopic recurrence after conventional surgery varies from 58% to 93% [28, 35, 36, 37]. The systematic review unfortunately found no published data on the ER rates after close or extended mesenteric resection [16]. In a survey of 34 surgeons, 71% were persuaded to change practice based on a reduction in endoscopic recurrence to 30% or less after 12 months.

The sample size calculation for the 2 × 2 factorial design assumes: 90% power; 5% (two‐sided) significance level; and estimated reduction in 1‐year endoscopic recurrence rates from 52.5% to 32.5%. Using the Freedman method a total of 112 recurrences are required [38]. After accounting for surgeon effects (assuming each of 12 sites would have 2 surgeons, an ICC of 0.01 and 15 patients per surgeon) and an attrition rate of 3%, the target sample size is 154 per group for each comparison.

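### The SAE proportion gets no effect estimate for either technique, and the plain Poisson model for SAE counts has no stated allowance for overdispersion and mislabels its ratio

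*Protocol article*

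**What the plan says.** All of this stands in the protocol article, Statistical methods, in the paragraph on secondary endpoints.

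- **SAE proportion.** SAE rates after randomisation "will be compared between the four randomised groups using a" chi-squared test, with a 95% CI for each of the four groups.
- **SAE count.** SAEs are totalled per patient, and the plan is to "compare counts using a Poisson generalised linear model (GLM) and reporting the risk ratio and associated 95% CIs". The text does not say whether this contrast is by four groups or by two factors. It mentions no dispersion term, robust variance or follow-up offset.
- **Other binary outcomes.** These are compared by factor (Kono-S vs standard; extended vs close) with multi-level logistic models, odds ratios and absolute risk differences.
- **Related safety outcomes.** Secondary outcomes lists anastomotic leak and other complications. If analysed as binary outcomes, they fall under the by-factor model.

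**The concern.** A reader choosing a technique needs to know whether Kono-S, or extended excision, changes the chance of a serious event, and by how much. A global test over four cells does not answer that. A significant result would not identify the technique, and a CI for each cell is not a CI for a difference. When harm follows one factor, the global test also spreads the same signal over 3 degrees of freedom instead of 1.

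The count model raises two separate questions. A Poisson model sets the variance equal to the mean. If one patient's complication is recorded as several SAEs, the variance exceeds the mean and the intervals are too short. And the exponentiated coefficient of a model for counts is a ratio of mean counts (a rate ratio once follow-up time is in the model). It is not a ratio of the risks of having an SAE.

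**Working it through.** **The plan's own figures.** The article gives no SAE rate, SAE power or dispersion, so only its group sizes can be checked.

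- Under proportional hazards, 52.5% and 32.5% at one year give HR = ln(0.675)/ln(0.475) = 0.528.
- Freedman events at 90% power and two-sided 5%: (1.960 + 1.282)² × ((1 + 0.528)/(1 − 0.528))² = 110.1, rounded up to 111. With HR rounded to 0.53 the result is 112, matching "Using the Freedman method a total of 112 recurrences are required".
- Mean event proportion = (0.525 + 0.325)/2 = 0.425. 111/0.425 = 261.2, or 131 per level.
- Design effect from "an ICC of 0.01 and 15 patients per surgeon": 1 + 14 × 0.01 = 1.14. With 3% attrition, 131 × 1.14/0.97 = 153.96, matching "the target sample size is 154 per group for each comparison".

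The SAE calculations therefore use 154 per factor level and 308/4 = 77 per cell.

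**Power for the SAE proportion (rates assumed).** The noncentrality is λ = Σ n(pᵢ − p̄)²/[p̄(1 − p̄)]. Power is the chance that a noncentral chi-squared variable exceeds 7.81 (3 df) or 3.84 (1 df).

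*Harm follows one factor, 10% vs 20%.* p̄ = 0.15 and p̄(1 − p̄) = 0.1275.

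- Four cells: λ = 77 × 4 × 0.05²/0.1275 = 6.04.
- By factor: λ = 154 × 2 × 0.05²/0.1275 = 6.04.

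The noncentrality is the same. Only the degrees of freedom differ.

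*Harm only in Kono-S + extended, 25% against 10% in the other three cells.* p̄ = 0.1375 and p̄(1 − p̄) = 0.1186.

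- Four cells: λ = 77 × (3 × 0.0375² + 0.1125²)/0.1186 = 10.96.
- By factor (10% vs 17.5%): λ = 154 × 2 × 0.0375²/0.1186 = 3.65.

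| Assumed pattern | Four groups, 3 df | By factor, 1 df |
|---|---|---|
| One factor, 5% vs 15% | 69% | 83% |
| One factor, 10% vs 20% | 52% | 69% |
| One factor, 15% vs 27% | 57% | 73% |
| One factor, 20% vs 30% | 37% | 53% |
| Combination arm only, 10% vs 25% | 80% | 48% |
| Combination arm only, 15% vs 30% | 69% | 39% |

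For 80% power the required noncentrality is 10.90 with 3 df and 7.85 with 1 df. The ratio is 1.39, so the four-group test needs about 39% more patients when harm follows one factor.

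**Poisson intervals (dispersion φ assumed).** If the variance is φ times the mean, the model standard error is 1/√φ of the true one, and a nominal 5% test rejects with probability 2[1 − Φ(1.96/√φ)].

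| φ | SE too small by | Coverage of 95% CI | Rejection at nominal 5% |
|---|---|---|---|
| 1 | 0% | 95.0% | 5.0% |
| 1.2 | 9% | 92.6% | 7.4% |
| 1.5 | 18% | 89.0% | 11.0% |
| 2 | 29% | 83.4% | 16.6% |

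A negative binomial simulation with 154 per level gave 10.7% at φ = 1.5 and about 16% at φ = 2.

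**The case against.** Four arguments on the other side carry weight.

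1. **The four-group test has a purpose.** The article stresses evaluating the techniques in combination, and harm confined to the combined arm is a reasonable worry. There the four-group test is clearly stronger. The expectation of no interaction is stated in the primary-analysis text on time to endoscopic recurrence, not for SAEs. This stands, and it is why the four-group results should be kept.
2. **Safety by factor is probably covered elsewhere.** A reader might infer that the plan wastes the factorial design's power for safety altogether. The article does not support that: leak and other complications appear to fall under the by-factor model. The gap is limited to the SAE proportion.
3. **Overdispersion is not shown.** A reader might infer that the Poisson intervals will be too narrow. The article gives no SAE rate or dispersion, and with φ near 1 coverage is nominal. A dispersion check or robust variance may also be in the analysis plan, which is not at hand, so its absence here is not an error. Nor does clustering by surgeon or centre make the case: randomisation is stratified by centre, the assumed ICC is 0.01, and such clustering does not by itself narrow the interval of a within-centre contrast. The relevant dependence is between repeat events in one patient.
4. **The offset matters little.** Table 1 lets the last adverse-event visit fall between 6 and 15 months, but the same window applies to every arm. Nothing suggests that follow-up differs by allocation.

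The 3-df criticism applies to the chi-squared test only, because the Poisson contrast is not specified. None of this supplies the missing per-technique SAE estimate or makes a ratio of counts a risk ratio.

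**Conclusion.** The point holds as a minor one on safety analysis. Two parts rest on the text alone: the SAE proportion has no stated effect estimate for either technique, unlike the other binary outcomes, and the count model's ratio is misnamed.

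The other two parts are conditional. The four-group test loses about 14 to 17 percentage points of power over the tabulated one-factor scenarios, and gains about 30 when harm lies only in the combination arm. All SAE rates here are assumed. The Poisson test rejects about 11% to 17% at a nominal 5% if the variance is 1.5 to 2 times the mean, which is also assumed. The primary analysis and the sample size are unaffected.

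**What to change.** - Add by-factor comparisons of the proportion of patients with at least one SAE. Use the logistic model and absolute risk differences already planned for binary outcomes, and report an interaction estimate with its CI.
- Keep the four-group comparison and per-group intervals beside it.
- State that the count model is fitted by factor, with robust standard errors or a negative binomial variance, and preferably with log follow-up time as an offset.
- Call the resulting ratio a rate ratio.

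This costs a few sentences in the analysis plan and no extra patients or data. The count intervals become somewhat wider: at φ = 1.5 to 2, by a factor of √1.5 = 1.22 to √2 = 1.41.

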### Data monitoring

The data monitoring and ethics committee (DMEC) will consist of an independent statistician and at least two independent physicians with research experience. The DMEC will review reports provided by the CTRU to assess the progress of the study, the safety data and the critical endpoint data as required. The DMEC will meet every 6 months. There will be no interim analyses (other than for the purposes of the blinded internal pilot) or definitive stopping guidelines, but the DMEC may request unblinded data or study termination on grounds of safety/futility.

### Harms

All Adverse Events (AEs) will be recorded on the adverse event report form, within the participant CRF. Sites are asked to enter all available information onto the study database as soon as possible after the site becomes aware of the event.

Once an SAE has been identified, a member of the site research team will complete an SAE form, notify the site's PI and send this to the CTRU.

SAEs which are related and unexpected will be reported to the sponsor and we will expedite these to the Research Ethics Committee (REC) within 15 days of becoming aware. The DMEC and TSC will also receive information on all AEs and SAEs.

